### Sample size and power

We conducted power analyses for teacher outcomes (the primary evaluation outcomes), assuming intention-to-treat analyses will be applied. Power analysis for aim three (contextual moderators) is not computed given the exploratory nature and lack of empirical evidence in this area of research. In cluster match-pair randomized designs, in addition to the usual study design parameters, the effect sizes detectable with 80% power of two-sided tests with level of significance α = 0.05 depend on the cluster (school) sizes (m), the intra-class correlation (ICC) associated with the cluster and the correlation between the schools within a pair (ρ). In technical terms, the clustering leads to a decrease of the actual sample size (N) by a factor called variance inflation factor (VIF = 1 + (m-1) ICC). The effective sample size (N*) in the case of cluster randomization is N* = N/VIF. Akin to a paired t-test, randomization within matched pairs can increase the power of a test, especially if ρ is large. Depending on the analytic model, the magnitude of the detectable effects can also be varied. For example, a model which includes covariates that account for some variance in the outcome, such as baseline levels of the outcome, would be more powerful (and would provide adequate power to detect smaller effects) than a model that does not make use of covariates [57].

We estimate the magnitude of the effects that are detectable with 10 schools, matched in five pairs, and 80 to 100 teachers (or eight to 10 teachers per school) with respect to post-intervention outcomes, at 80% power of a 2-sided test with level of significance α = 0.05. The following assumptions are made in those computations: 1) the baseline values of the outcome and other baseline covariates in the model account for 20 to 50% of variance of the post-intervention outcomes (estimated variance obtained from trials conducted in the United States); 2) correlations of the outcome measures between schools within a pair (ρ) will be high, ranging from 0.50 to 0.70; and 3) ICCs associated with clustering of teachers within a school will range from 0 to 0.10. The detectable effects (Cohen’s d) would be d = 0.11 to 0.29. The proposed study will have sufficient power to detect impact on teacher outcomes that are meaningful and realistic.

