### The mental health intervention

The EBP that we apply in this study is ParentCorps. ParentCorps is a culturally-informed, multicomponent intervention for young children that promotes high-quality learning environments at home and school (such as positive parent-child and teacher-child interactions and effective behavioral management practices), resulting in meaningful educational, developmental and health benefits for children, especially those who are behaviorally dysregulated (for example impulsive or inattentive) in early childhood [39–42]. ParentCorps was built on an extensive body of cross-cultural parenting and child developmental research [11, 39, 42–47]. The program includes three core intervention components. The ‘Professional Development’ component aims to increase knowledge, motivation and capacity to employ evidence-based practices for creating positive teacher-child interactions and strong home-school connections, and for implementing the programs for parents and students. Professional Development includes the ParentCorps ‘FUNdamentals’ course (four days large-group experiential training and two additional days of separate training for mental health professionals in implementing the ‘Program for Parents’ and teachers in implementing ‘Program for Students’) and ‘Coaching’ (providing *in vivo* support to trainees to enhance their ability to identify and address the needs of students and to employ evidence-based practices in daily interactions with students and parents). The ‘Program for Parents’ component (consisting of 14 two-hour sessions) aims to increase parent knowledge, motivation and capacity to use a set of evidence-based parenting practices (parallel to those presented in Professional Development). The ‘Program for Students’ component (consisting of 14 two-hour sessions) aims to increase children’s knowledge, motivation and capacity to use social-emotional and behavior regulation skills through lessons, activities and a systematic approach to behavior management. In two cluster (school) randomized controlled trials (RCTs) with low-income, minority students in New York City in the United States, ParentCorps has shown to be highly acceptable to ethnically diverse populations in poor urban communities, and has had significant, robust and sustained effects on all targeted teacher, parent and child outcomes [39–41, 48–50]. These include effects on teachers’ utilization of proactive and positive reinforcement strategies, positive classroom climate and confidence in engaging families (Cohen’s ds ranged from 0.42 to 0.85, comparable to the range 0.51 to 1.29 reported in the literature [51]); parents’ utilization of effective parenting practices, involvement in child education and parenting knowledge (Cohen’s ds ranged from 0.16 to 0.50, compared to 0.30 to 0.88 reported in the literature [52]); and early childhood students’ social-emotional (adaptive behaviors, externalizing and internalizing problems) and academic outcomes (Cohen’s ds ranged from 0.25 to 0.56, compared to 0.24 to 0.81 reported in the literature [52–55]).

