### Participants

The study aims to enroll primary school and all early childhood teachers, including nursery pre-kindergarten and kindergarten, and primary one, two and three (first to third grades), serving students between four and eight-years-old. Based on our prior work, Ugandan primary schools have, on average, about 700 students (ranging from 100 to 2,300, SD = 440), 23 teachers (ranging from 7 to 56, SD = 13) and 54 students in each class (ranging from 15 to 90, SD = 21). The schools have on average six to eight early childhood teachers (for four to eight-year-olds). We anticipate that 80 to 100 early childhood teachers from the 10 study schools (40 to 50 teachers in each condition) will participate in the RCT, and estimate that more than 3,200 children across conditions (including waitlist control schools at the end of the trial) will be impacted during the study period ([name] and [name], unpublished observations). Although the trial is carried out in schools, parents, guardians and students are not considered subjects of this study. They will not participate in any research activity, therefore, consent of parents and guardians will not be obtained.

The study is being conducted by investigators from the United States and Uganda. All study recruitment and assessment procedures will be conducted by Ugandan research staff. Principals will be informed about the randomization procedures, study timeline, teacher assessments and intervention procedures (including immediate provision in the intervention schools and delayed provision in the control schools). Once principals agree to participate and sign a written agreement, teachers from the schools will be approached by research staff to assess their interest. Teachers will provide written informed consent and will be informed that they have the right to refuse to participate in the study, even though the principals and other teachers agree (with no negative consequences).

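### The detectable effects of d = 0.11 to 0.29 do not follow from the plan's own inputs, which give roughly 0.40 to 0.86 depending on the analysis

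*Protocol article*

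**What the plan says.** Sample size and power treats teacher outcomes as the primary evaluation outcomes and sets the calculation "at 80% power of a 2-sided test with level of significance α = 0.05". The design is "10 schools, matched in five pairs, and 80 to 100 teachers (or eight to 10 teachers per school"). The Participants section splits the teachers equally: "80 to 100 early childhood teachers from the 10 study schools (40 to 50 teachers in each condition").

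Three assumptions follow. Baseline values and other covariates explain 20 to 50% of the outcome variance. The correlations between paired schools "will be high, ranging from 0.50 to 0.70". The clustering assumption is that "ICCs associated with clustering of teachers within a school will range from 0 to 0.10". The section gives VIF = 1 + (m-1)ICC and N* = N/VIF, and likens the matching to a paired t-test. It gives no formula that combines the covariate and pairing gains, and it does not mention degrees of freedom.

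The result is that the detectable effects "would be d = 0.11 to 0.29. The proposed study will have sufficient power" for effects described as meaningful and realistic. For comparison, the section on the mental health intervention reports that teacher effects in the earlier US trials had Cohen's "ds ranged from 0.42 to 0.85, comparable to the range 0.51 to 1.29 reported in the literature".

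The analysis for aim two is a linear mixed model that adjusts for school nesting. It names no pair effect.

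**The concern.** A detectable effect of 0.11 standard deviations is very small for a two-arm comparison of 40 to 50 teachers per arm, even before clustering. The design has only 10 randomised units, which should push the detectable effect up.

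This is the only power statement for the primary outcomes. Read as written, it implies that even the smallest US teacher effect (0.42) is comfortably powered and that effects a quarter of that size are within reach. A reader who relies on it could take a non-significant result as evidence against small effects that the trial has little chance of detecting.

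**Working it through.** **Inputs** (all from Sample size and power): two-sided alpha 0.05; power 80%; 5 pairs; m = 8 to 10 teachers per school, so N = 80 to 100; R² = 0.2 to 0.5; rho = 0.5 to 0.7; ICC = 0 to 0.10. Detectable d = multiplier × SE, in units of the unadjusted SD. The multiplier for 80% power is 1.960 + 0.842 = 2.802 with normal quantiles, 3.761 from the noncentral t with 4 df (five pairs), and 3.201 with 8 df (10 unpaired schools).

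**1. Attempt to reproduce 0.11 to 0.29.** The nearest match comes from a variance without the factor 4 that a two-arm comparison of total size N needs, and with rho applied to all variance: d = 2.802 × √[(1-R²)(1-rho)VIF/N].
- Best corner (N = 100, R² = 0.5, rho = 0.7, ICC = 0): 2.802 × √(0.5 × 0.3/100) = 0.109. This matches the lower end.
- Worst corner (N = 80, R² = 0.2, rho = 0.5, ICC = 0.10, VIF = 1.7): 2.802 × √(0.8 × 0.5 × 1.7/80) = 0.258. This is not 0.29.
- With R² = 0, the worst corner becomes 2.802 × √(0.5 × 1.7/80) = 0.289. This matches the upper end, but R² = 0 lies outside the stated 20 to 50%.

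**2. A bound that needs no view on pairing.** With 100 individually randomised teachers, R² = 0.5 and ICC = 0: 2.802 × √(4 × 0.5/100) = 0.396. At ICC = 0 there is no between-school variance for matching to remove. Reaching d = 0.11 under these conditions needs 2.802² × 4 × 0.5/0.11², or about 1,300 teachers.

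**3. Pairing acts on between-school variance only.** Var = 2(1-R²)[ICC(1-rho) + (1-ICC)/m]/5.
- Best corner: 2 × 0.5 × (1/10)/5 = 0.020, SE = 0.141.
- Worst corner: 2 × 0.8 × (0.05 + 0.1125)/5 = 0.052, SE = 0.228.

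**4. Unpaired.** Var = (4/N)(1-R²)VIF. The best corner is again 0.020. The worst is (4/80) × 0.8 × 1.7 = 0.068, SE = 0.261.

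**5. Most lenient reading: rho cuts the whole variance.** Var = (4/N)(1-R²)(1-rho)VIF.
- Best corner: 0.04 × 0.5 × 0.3 = 0.006, SE = 0.077.
- Worst corner: 0.05 × 0.8 × 0.5 × 1.7 = 0.034, SE = 0.184.

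| Reading | Quantiles | Detectable d |
|---|---|---|
| Stated in the article | not given | 0.11 to 0.29 |
| Pairing on between-school variance | normal | 0.40 to 0.64 |
| Same | t, 4 df | 0.53 to 0.86 |
| Unpaired school-level | t, 8 df | 0.45 to 0.84 |
| rho on all variance | normal | 0.22 to 0.52 |
| Same | t, 4 df | 0.29 to 0.69 |

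**6. Is the lenient reading compatible with the stated ICCs?** Observed school means can correlate at most m × ICC/VIF. This is 0 at ICC = 0. At ICC = 0.10 it is 0.8/1.7 = 0.47 for m = 8 and 1.0/1.9 = 0.53 for m = 10. A correlation of 0.50 to 0.70 between observed school means is therefore almost wholly out of reach.

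**7. Power with the step 3 variance** (worst to best corner).

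| True d | Normal | t, 4 df |
|---|---|---|
| 0.29 | 25 to 54% | 17 to 35% |
| 0.42 | 45 to 84% | 29 to 61% |
| 0.50 | 59 to 94% | 39 to 75% |
| 0.85 | 96% or more | 79 to 99% |

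At d = 0.11, power in the best corner is 12% (normal) or 9% (4 df).

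**The case against.** The article does not say which variance component rho refers to, and its paired t-test analogy could be read as letting rho shrink the whole variance. On that reading the corrected range starts at 0.22 and overlaps the upper part of the stated one. This stands as an ambiguity. It does not rescue the figure: both ends are still nearly twice those stated, and the reading conflicts with the article's own ICCs (step 6).

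The 4-df range assumes that pairs are analysed, whereas the analysis for aim two names school nesting only. That also stands. The 4-df range should not be presented as the single right answer, and the unpaired 8-df range is closer to the model described.

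Three stronger conclusions are tempting, and the document does not support them.
- A reader might infer that the authors dropped the two-arm factor of 4. This is a likely explanation but not a proven one: it matches the lower end, but matches the upper end only with R² = 0, and the article shows no combined formula.
- A reader might infer that the trial cannot detect moderate effects. Power of 39 to 94% at d = 0.50 contradicts that as a general statement.
- A reader might call the sufficiency sentence simply false. It speaks of meaningful and realistic effects, and the corrected ranges overlap both the US effects and the literature range of 0.51 to 1.29. The sentence is unsupported as derived and doubtful near 0.42, but power is good at the upper end.

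**Conclusion.** The stated range is wrong by about a factor of two on the reading most favourable to the plan, and by more on the reading that agrees with the plan's ICCs. The coherent ranges are 0.40 to 0.64 (normal), 0.53 to 0.86 (paired, 4 df) and 0.45 to 0.84 (unpaired, 8 df). They rest on the article's own inputs, on equal school sizes and on R² reducing between-school and within-school variance alike. The bound of 0.396 in step 2 needs only N = 100, R² = 0.5 and no clustering, which is enough to rule out 0.11 once pairing has no between-school variance to act on.

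The inputs may themselves be favourable. The Participants section also gives an average of six to eight early childhood teachers per school. If that held in the study schools, there would be 60 to 80 teachers rather than 80 to 100, and the detectable effects would be larger. The conclusion does not depend on this.

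The error lies in the power statement. It does not make the design or the planned analysis invalid.

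**What to change.** In Sample size and power, replace 0.11 to 0.29 with the range recomputed for the analysis that will be used. Show the variance formula, how rho is defined, and the degrees of freedom: 4 if pairs are modelled, 8 if they are not.

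Qualify the sufficiency sentence. It should say that power is adequate only for effects in the middle to upper part of the US range (0.42 to 0.85); that with pairing power at d = 0.42 is about 29 to 61% (4 df) or 45 to 84% (normal), or the matching figures if pairs are not modelled; and that a null result cannot exclude smaller effects.

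The cost is a correction to one paragraph and a less favourable stated detectable effect. No extra schools or teachers and no change to the conduct of the trial are needed.

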### Description of the intervention

To implement the intervention, a ‘train the trainer’ model was employed. Three Ugandan mental health professionals spent 10 days in the United States at ParentCorps Academy. Upon return to Uganda, they facilitated training of their peers (seven mental health professionals) along with 10 hours of video conference support from ParentCorps Academy. This group of 10 mental health professionals, led by the three original trainees, is responsible for the implementation of ParentCorps FUNdamentals. All trained mental health professionals are responsible for implementing Coaching for teachers. The mental health professionals will participate in 14 group supervision calls with ParentCorps Academy over the course of the implementation phase of the study (or on the week they provide coaching sessions to the teachers).

#### Intervention group

For this study, intervention is limited to Professional Development (described above). Because the plan was to wait to implement the Programs for Parents and Programs for Students until after the completion of this initial study, the two-day training of ParentCorps FUNdamentals that are meant to train mental health professionals and teachers to implement the programs with fidelity will not be included. FUNdamentals has been ‘repackaged’ to be delivered to Ugandan teachers by Ugandan mental health professionals over a five-day period. As in the version implemented in the United States, FUNdamentals is a large-group experiential training series aimed at building knowledge, evidence-based skills, shared language, motivation for change and a sense of community. Over the five days, in a safe and supportive environment, participants are asked to reflect on their assumptions (positive and negative) about parents and students and to connect those assumptions to their current practices and capacity to help children succeed. Under this learning environment, they also learn a series of evidence-based behavioral management skills. Coaching sessions provide support for teachers to employ evidence-based practices in daily interactions with students and parents, and helps teachers to identify and address the needs of students without the requisite self-regulation skills for school success. The Coaching model (one-to-one professional to teacher ratio in the United States) was revised to be delivered by a pair of mental health professionals to groups of early childhood teachers at the school during school breaks or after school hours because of the lower cost and potential benefits from working as a group in a collective culture (gaining support and opportunities to learn from one another). Based on feedback from school leaders, 14 group coaching sessions (one to two hours duration) were designed to take place over a six-month period, decreasing in frequency over time (eight weekly sessions, four bi-weekly sessions and two monthly sessions).

### Study measures

This study utilizes a multi-method and multi-informant approach to measurement. Data will be collected from teachers, mental health professionals and objective blind observation (video tape coding). The measurement strategy was developed under the Reach/Efficacy-Adoption/ Implementation/Maintenance (RE-AIM) evaluation framework [58, 59]. The RE-AIM framework conceptualizes the public health impact of an intervention as a function of five dimensions: reach, effectiveness, adoption, implementation and maintenance. The dimensions that are captured in the RE-AIM are consistent with the constructs described in our implementation conceptual framework.

#### Reach

Early childhood teachers will be characterized in terms of demographics, attitudes about use of evidence-based practices and students, parents and school leadership [60, 61], self-efficacy [62] and motivation for change [63].

#### Effectiveness

Teacher practices (behavioral management practices and classroom climate) will be assessed by self-report [64] and classroom observations. The Teacher Instructional Practices and Processes System, a classroom observation coding system designed to assess climate, instructional practices and processes for use in schools in developing countries (TIPPS) [65], will be applied. Two trained observers, who are masked to the study condition, will conduct live observations of teachers for a 20-minute period during a lesson. Observers will rate each teacher’s behavior independently. Effectiveness data will be collected before intervention and immediately after intervention.

#### Adoption

To characterize the target setting (school inner setting), data will be collected at baseline from two sources. School principals will complete a School Environment Questionnaire [66] that assesses school demographics, resources and school climate. Teachers will complete a School Climate Questionnaire [67] that measures principals’ leadership, cohesion, communication, stress and autonomy.

#### Implementation

Four domains of implementation fidelity will be assessed. Adherence, the extent to which the mental health professionals deliver the core intervention content and as per program guidelines, will be evaluated based on ParentCorps’ integrity checklists completed by the implementer and videotapes and/or audiotapes of FUNdamentals (all five days) and coaching sessions (five of 14) coded by ParentCorps Academy faculty. Quality of program implementation will be assessed based on teacher satisfaction with the Professional Development and ratings of coaches’ competence. Engagement will be evaluated with two ParentCorps measures of knowledge and practice [40]. Level of knowledge improvement from pre- to post-training will be used as indicators for level of engagement. Exposure will be measured by attendance at ParentCorps FUNdamentals (five days) and coaching sessions (14 sessions).

#### Maintenance

Teacher practices during the new school year (about seven months after the intervention) will be measured via self-report and classroom observations as described above.

### Statistical methods

#### Preliminary analyses

Baseline equivalence between intervention and control schools will be examined. Missing data patterns and distribution of the study variables will be inspected prior to any outcome analyses. In addition, psychometric properties of study measures will be inspected, and only measures with adequate reliability and validity will be applied for subsequent study. For measures that evaluate similar constructs, composite scales will be created (to minimize number of analyses).

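### The composite rule has no exception for informant or masking, so read literally it lets masked classroom observation be averaged with teacher self-report

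*Protocol article*

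**What the plan says.** All references are to the protocol article.

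- **Effectiveness** defines one outcome and two sources: "Teacher practices (behavioral management practices and classroom climate) will be assessed by self-report [64] and classroom observations". The observation arm of this is carried out by "Two trained observers, who are masked to the study condition". The instrument is described as "a classroom observation coding system designed to assess climate, instructional practices and processes for use in schools in developing countries (TIPPS".
- **Maintenance** keeps both sources at follow-up: practices in the new school year "will be measured via self-report and classroom observations as described above".
- **Sample size and power** refers to "teacher outcomes (the primary evaluation outcomes" as a group and singles out no instrument.
- **Preliminary analyses** first screens the instruments ("only measures with adequate reliability and validity will be applied for subsequent study") and then gives the rule at issue: "For measures that evaluate similar constructs, composite scales will be created (to minimize number of analyses".
- **Analyses for aim two** models teacher practices at time two on intervention, adjusting for time one, again without naming an instrument.

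**The concern.** The composite rule is worded as something that will be done. Its only stated reason is to reduce the number of analyses, and it does not separate sources. Self-report and observation of teacher practices sit under one outcome label, so they fall within it on a plain reading.

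The two sources differ in the respect that matters most in a trial with an untreated waitlist. The observers are masked. The teachers, by inference, are not: those in intervention schools attend five training days and 14 coaching sessions on the very practices they then rate, while waitlist teachers receive nothing until after the post-assessment. If training changes how teachers describe their practice without changing the practice, self-report moves and masked observation does not. Kept apart, the two results would show this to a reader. Averaged, they would not, and a positive composite could not be read with confidence as a change in the classroom. Adjusting for time one scores does not help, because the differential reporting arises after randomization.

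**Working it through.** **Step 1. Does the rule reach these two measures?**

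| Question | What the article gives |
|---|---|
| Same construct? | One outcome label covers both sources (Effectiveness). Climate is named in the outcome and again among what TIPPS assesses. Behavioral management is named in the outcome but not in the description of TIPPS. |
| Is combining optional? | No. The wording is that composites will be created. |
| Any exception for informant or masking? | None stated. |
| Are the sources kept apart later? | Not stated. The aim two model refers only to teacher practices. |
| Is a cross-source composite named? | No. |

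The rule therefore reaches at least the climate scores, and arguably the whole teacher-practices outcome, but the article does not say it will be used in that way.

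**Step 2. Are the self-reporters unmasked?** The article does not say so. The inference rests on the waitlist design and on the delivery of the programme: "Exposure will be measured by attendance at ParentCorps FUNdamentals (five days) and coaching sessions (14 sessions". Teachers who attend know that they attended.

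**Step 3. What would averaging do?** No figure in the plan needs reproducing here; this is an illustration. Assumptions, none of them from the documents: both scores are scaled to unit SD, weights are equal, the correlation between them is r, true change in practice is zero, and self-report in the intervention arm is shifted by b SD.

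- Composite = (self-report + observation)/2.
- Shift in its mean = b/2.
- Its SD = sqrt((1 + r)/2).
- Standardized shift = (b/2)/sqrt((1 + r)/2).

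With r = 0.3 the SD is sqrt(0.65) = 0.806:

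- b = 0.2: 0.10/0.806 = 0.12
- b = 0.4: 0.20/0.806 = 0.25

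Sensitivity to r at b = 0.4: r = 0.1 gives 0.20/sqrt(0.55) = 0.27, and r = 0.5 gives 0.20/sqrt(0.75) = 0.23. The choice of r matters little; the assumed b drives the result.

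**Step 4. Compare with the plan.** Sample size and power states detectable effects of d = 0.11 to 0.29. Shifts of 0.12 and 0.25 lie inside that range.

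**Step 5. The alternative.** With the sources analysed separately, the same self-report shift contributes 0 to the masked observation score.

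**The case against.** The strongest reply is that the article never says the two sources will be merged. The rule is a general sentence that also covers attitudes, self-efficacy, school climate and fidelity scales, where composites within one source are the ordinary reading. The article describes its measurement as multi-method and multi-informant and lists observation as a source of its own. This stands: a reader might infer that the plan has decided to pool, and the text does not support that.

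Second, a reader might infer that the composite is how reporting bias gets into the primary outcomes. It is not. Self-report is already one of the primary teacher outcomes, so that bias is present with or without pooling. The harm specific to pooling is narrower: the masked score stops being a masked score.

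Third, two measures correlating at 0.3 make a poor composite. By Spearman-Brown its reliability is 2(0.3)/(1 + 0.3) = 0.46, which sits badly with a section that asks for adequate reliability. That makes pooling less likely in the illustrated case. It does not rule it out, because the screen is applied to measures and not expressly to composites. Nor does a reliability screen guard against bias, since a biased scale can be highly reliable.

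Fourth, the data on which measures are screened, and the exact list of composites, are details that a condensed article may leave to a fuller document; their absence is not held against the plan. A reader might also carry the point to aim three, where teacher satisfaction is one of the fidelity indicators. That argument is weak: self-report kept separate would share more informant variance with satisfaction than a composite would, and the article calls that aim exploratory.

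**Conclusion.** The point holds as a defect in a stated rule. As worded, the rule directs, or at the least permits, combining a masked observation score with self-report from teachers who can be presumed to know their condition. Following it literally would give a worse primary analysis than keeping the sources apart, and the only gain offered is fewer analyses.

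The size is not known. A composite shift of about 0.12 to 0.25 SD follows from an assumed reporting shift of 0.2 to 0.4 SD, an assumed correlation of 0.3, equal weights and no true change. It shows that a moderate reporting shift could resemble an effect the plan says it can detect. It does not show that such a shift will occur, and it takes the stated range of 0.11 to 0.29 as given.

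**What to change.** In Preliminary analyses, state that composites are formed only within one informant and never across teacher self-report and classroom observation. In Analyses for aim two, name the masked TIPPS score at time two as the lead teacher outcome, with self-report analysed separately as secondary.

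This changes wording only. The cost is one or two more models, plus the loss of any precision a cross-source composite might have added. Trial status reports that the data were not yet cleaned or finalized, so at publication the change could still be made before the outcome analysis.
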